**A. Introduction**

Bacterial vaginosis, the most common bacterial genital infection in women of reproductive age has been linked to considerable gynecologic and obstetric morbidity. Recent studies demonstrate that BV may be a cofactor in acquisition of human immunodeficiency virus type (HIV) infection. 1-3. The highest prevalence of BV has been in sub-Saharan Africa where HIV infection is also common 2,3. It has been postulated that BV may increase susceptibility to HIV infection by a variety of mechanisms including possibly altering the host’s defense system through the absence of the normal H2O2-producing vaginal lactobacillus (which allow to maintain the natural acidic pH of the vagina), with loss of the protective myeloperoxidase halide-hydrogen peroxide system 4, and by production of metabolic by-products that may increase HIV replication 5,6 or activate target cells for HIV infection 7. If any of these hypotheses are correct, reduction of BV prevalence could significantly reduce female HIV acquisition. The high prevalence of BV in sub-Saharan Africa remains unexplained. Though considerable evidence supports sexual transmission of BV, factors like clothing, climate and hygiene may influence vaginal flora. Of the various risk factors associated with BV, the contribution of each to causing BV may vary depending on hygienic, sexual and other practices 8. BV treatment with metronidazole was first found to be to be effective in the initial clearing of symptoms and signs of BV 9, but has since proven disappointing even in industrialized countries, since recurrence rates reach 40% within 3 to 6 months after treatment with oral or intravaginal medication 10,11.In Uganda, administration of metronidazole, azithromycin and ciprofloxacin to large populations of adults of reproductive age every 10-months did not reduce the prevalence of BV below 50% 12.

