**C. Methods**

**C.1 Overview**

At the Zimbabwe site, self-collected vaginal swabs will be collected on the 500 women enrolled in the RCT at their enrollment visit and every three months per study protocol. Data on recent vaginal hygiene and other practices that may affect vaginal microflora will be collected on an additional questionnaire at every follow-up visit. Since the site will enroll over 2,000 women over the course of the randomized trial, enrollment for the BV component will take place at one of the three recruitment centers, and will be closed once the full sample size has been attained.

To study Aim II, 500 women with symptomatic BV will be required. Unfortunately, since we will not be able to perform vaginal Gram stains in real-time, the initial diagnosis of BV will be made using the modified Amsel’s criteria (pH > 4.7, positive whiff test and clue cells on wet mount). Those diagnosed with BV will receive a 5-day course of metronidazole 400 mg three times per day. Vaginal Gram stains will also be collected. Only women with a Nugent score  7 and with 3 of 3 Amsel’s criteria will be analyzed. Women enrolled in Aim II will have a vaginal Gram stain repeated on a self-collected vaginal swab three months after treatment. The prevalence of BV after three months will serve as the primary endpoint for this aim.

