**C.2.2.3 Aim 2 sample size**

We assume that a minimum 5% of participants will present with symptomatic BV at every visit. Given the projected sample of 2200 women for the Zimbabwe (and a total of nearly 13,000 follow-up visits), this implies that approximately 660 diagnosed cases of symptomatic BV should be observed. The primary outcome for this aim will be recurrence of BV within three months following treatment for symptomatic disease. We assume that recurrence rates will be compared across arms on an intent-to-treat basis using a chi-squared statistic, and that loss-to-follow up rates in a three month visit cycle will not exceed 5%. Given these assumptions, and assuming three-month recurrence rates among women receiving only condoms in the range 0.1 - 0.2, a total sample size of 500 women will provide 80% power to detect a 33% reduction in recurrence associated with treatment at the 5% significance level.

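### BV sub-study Aim 2: 500 women in total give about 25% to 49% power on the stated assumptions, not 80%

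*Protocol*

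**What the plan says.** Appendix 16.1 (bacterial vaginosis sub-study), section C.2.2.3, sizes Aim 2, the comparison of BV recurrence after treatment between the two randomised arms. It states that "a total sample size of 500 women will provide 80% power to detect a 33% reduction in recurrence", "at the 5% significance level", and gives the control rate by "assuming three-month recurrence rates among women receiving only condoms in the range 0.1 - 0.2". The comparison is by chi-squared test (also stated in C.2.2.4), and loss over a three-month cycle is taken to be no more than 5%. The same section expects about 660 symptomatic cases.

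The overview in C.1 repeats the number: "To study Aim II, 500 women with symptomatic BV will be required".

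The appendix's introduction (section A) gives a different order of recurrence from the literature: "recurrence rates reach 40% within 3 to 6 months after treatment with oral or intravaginal medication".

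**The concern.** All the main inputs to the power statement are printed, so it can be recalculated. A one-third cut from a base of 10% to 20% is an absolute difference of only 3.3 to 6.6 percentage points. About 250 women per arm looks too few to detect that with 80% power.

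If the power is far lower, Aim 2 could well miss the effect it was sized for. A non-significant result could then be taken as reasonable evidence against a one-third reduction, which the data could not support. This is separate from whether 500 eligible women can be found.

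**Working it through.** **Inputs**
- Total 500 women, target power 80%, 33% reduction, 5% level, control rate 0.1 to 0.2, loss at most 5%: Appendix 16.1, C.2.2.3.
- Chi-squared test of two proportions: C.2.2.3 and C.2.2.4.
- Allocation 1:1: the parent trial, Study Summary.
- Sidedness is not stated for Aim 2. Two-sided is assumed, as Aim 1 of the same appendix states (C.2.2.1); one-sided is also tried.
- The 33% is read as relative (risk ratio 0.67), because an absolute drop of 33 points is impossible from 10% to 20%.

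**Formula**

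With control risk p0, intervention risk p1 = 0.67 p0, mean risk m = (p0 + p1)/2 and n evaluable women per arm:

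power = Φ{ [ (p0 − p1) − 1.96 √(2m(1 − m)/n) ] / √( [p0(1 − p0) + p1(1 − p1)]/n ) }

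**The plan's figure, after its own 5% loss** (n = 250 × 0.95 = 237.5)

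- p0 = 0.20, p1 = 0.134, m = 0.167. Null standard error √(0.27822/237.5) = 0.03423, times 1.96 = 0.06708. Alternative standard error √(0.27604/237.5) = 0.03409. Power = Φ[(0.066 − 0.06708)/0.03409] = Φ(−0.03) = 0.49.
- p0 = 0.10, p1 = 0.067, m = 0.0835. Null standard error √(0.15306/237.5) = 0.02539, times 1.96 = 0.04976. Alternative standard error √(0.15251/237.5) = 0.02534. Power = Φ[(0.033 − 0.04976)/0.02534] = Φ(−0.66) = 0.25.

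The stated 80% is not reproduced. A simulation of 200,000 runs at 237 per arm gave 0.255 and 0.492.

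**Other readings of the same sentence**

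| Reading | p0 = 0.10 | p0 = 0.15 | p0 = 0.20 |
|---|---|---|---|
| 500 total, 5% loss, two-sided | 25% | 37% | 49% |
| 500 total, no loss, two-sided | 27% | 39% | 51% |
| 500 total, no loss, one-sided | 38% | 51% | 63% |
| All 660 expected cases, no loss, two-sided | 33% | 48% | 62% |
| All 660 expected cases, no loss, one-sided | 46% | 61% | 74% |
| 500 per arm, no loss, two-sided | 47% | 66% | 80% |

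A continuity correction, unpooled variance, the arcsine approximation, 33% read as an odds ratio or as an increase, and 0.1 to 0.2 read as the treated-arm rate were also tried. None gives 80% with 500 in total. For 500 in total to give 80% two-sided, control recurrence would have to be about 0.34 without loss or 0.35 with it.

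**Numbers that would give 80%** (two-sided)

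n per arm = [1.96 √(2m(1 − m)) + 0.8416 √(p0(1 − p0) + p1(1 − p1))]² / (p0 − p1)²

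- p0 = 0.20: (1.0338 + 0.4422)²/0.004356 = 500.1, so 501 evaluable per arm (1,002 in total). With 5% loss, 501/0.95 = 527.4, so 528 enrolled per arm.
- p0 = 0.10: (0.7668 + 0.3287)²/0.001089 = 1,102 evaluable per arm (2,204 in total). With 5% loss, 1,102/0.95 = 1,160 enrolled per arm.

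**What 500 women can detect** (80% power, two-sided, 5% loss)

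Solving the power formula for p1 gives 0.036 when p0 = 0.10, a reduction of about 64%. It gives 0.107 when p0 = 0.20, a reduction of about 46%.

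**At the literature figure in section A**

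If control recurrence at three months were 0.40, the same 500 women with 5% loss would have about 86% power for a 33% reduction, and the detectable reduction would be about 30%.

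**The case against.** The core calculation has no good rebuttal: no reading of the stated inputs reaches 80%, and the wording of the total and of the recurrence range is legible. The objections that carry weight concern what surrounds it.

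- **The per-arm explanation is an inference.** It rests on a match at one end of the range. At 0.1, 500 per arm still gives only 47%, and 500 enrolled per arm with 5% loss gives 78% even at 0.2. Aim 1 also uses 250 women per arm, so the origin of the 500 cannot be known from the document. This stands. The explanation is only a possibility, and the error does not depend on it.
- **The 40% is not a contradiction.** It is an upper figure over three to six months from outside literature, while Aim 2 assumes a three-month rate in the condom-only arm. This also stands. The figure is context: it shows that the claim hinges on the assumed rate.
- **5% is a ceiling on loss.** With no loss, power at 0.2 is 51%, so the chance of missing the effect exceeds one half everywhere in the range except at its very top with almost no loss.
- **The stakes are limited.** This is the second aim of an ancillary study at one site. That bears on its weight within the whole trial, not on whether the printed power is correct.

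**Conclusion.** The concern holds. The power statement for Aim 2 is wrong on its own inputs: two-sided power after the assumed loss is 25% to 49% over the stated recurrence range, against 80% claimed. The calculation assumes 1:1 allocation, a two-sided 5% test and a relative reduction of 33%. The conclusion survives a one-sided test (at most 63%), zero loss (at most 51% two-sided) and use of all 660 expected cases (at most 74%, one-sided without loss). The paragraph must be corrected for the sub-study's own claim to stand; the trial's primary analysis and sample size are not touched.

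**What to change.** Rewrite the power sentence in C.2.2.3 to say that, with 500 women in total, 5% loss and a two-sided 5% chi-squared test, power for a 33% reduction is about 25% at 10% recurrence and 49% at 20%, and that the reductions detectable at 80% power are about 64% and 46%. State that the test is two-sided.

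In the same paragraph, justify the 0.1 to 0.2 range beside the 40% cited in section A. If a three-month rate near 40% can be supported, add that power would be about 86% and the detectable reduction about 30%. Align the 500 in C.1 with whatever is adopted.

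Optionally, present Aim 2 as an estimate with a confidence interval unless the higher rate is adopted.

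The cost is the wording of one paragraph and a less favourable stated power. No further women or procedures are needed. Keeping 80% power for a 33% reduction within the stated range would instead need at least 1,002 evaluable women, more than the 660 cases the section expects.

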**C.2.2.4 Aim 2 major endpoints**

The primary outcome for Aim 2 will be a binary indicator of BV recurrence observed three-months after treatment. Recurrence proportions will be compared across treatment arms using a chi-squared test.

**Introduction**

The randomized controlled trial of diaphragm use in Zimbabwean women will determine whether provision of diaphragms reduces the rate of male-to-female vaginal HIV transmission. This study is also an unparalleled opportunity to examine the role of the diaphragm in reducing human papillomavirus (HPV) infection. The role of HPV in the development of cervical cancer is well supported by extensive epidemiologic and biological data. As the most prevalent sexually transmitted disease worldwide, genital HPV infection places millions of women at risk for cervical cancer. No randomized controlled trials have been performed to determine the effect of diaphragms on any sexually transmitted infection, including HPV. We propose that diaphragm provision will decrease HPV incidence and persistence, and hence reduce risk of cervical cancer. This straightforward hypothesis can be readily tested with the addition of a limited number of tests to the existing Diaphragm Intervention Study. If substantiated, we may be able to offer women worldwide a simple, affordable, readily available intervention to reduce the risk of cervical cancer.

**Study Hypotheses and Specific Aims**

***1. Diaphragm use will decrease the incidence of HPV.*** We propose to collect samples at each visit for HPV testing and typing by PCR in the randomized cohort of Zimbabwean women. We will determine the effect of diaphragm use on the rates of incident infections.

***2. Diaphragm use will decrease the persistence of HPV.*** We will determine the effect of diaphragm use on persistence of HPV in women found to be positive at enrollment.

***3. Diaphragm use will decrease the incidence of cervical cytologic abnormalities.*** Women will receive cytologic evaluation at enrollment and exit. We will determine the effect of diaphragm use on the rates of cytologic abnormalities.

***4. HPV infection increases the risk of male-to-female vaginal HIV transmission.*** We hypothesize that HPV infection will result in recruitment of a local immune response, which might place women at increased risk for heterosexual HIV acquisition. We will compare the rates of HIV acquisition in HPV-negative *versus* HPV-positive women. In addition, we will examine the effect of HPV viral load on HIV transmission.

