# 1 Trial Abstract

This multi-site randomized, controlled trial will measure the effectiveness of the diaphragm in preventing heterosexual acquisition of HIV infection among women. This Phase III study is powered to detect effectiveness (biological efficacy combined with adherence) of 33 percent. Women in South Africa and Zimbabwe (N=5,000) at risk of contracting HIV are invited to participate and are followed for up to 24 months, with a total study duration of 4 years. All women receive safer-sex counseling, free male condoms and diagnosis and treatment of sexually transmitted infections (STIs). Half of the participants are selected randomly to receive an Ortho All-Flex latex diaphragm and Replens lubricant gel. We are assessing whether women using diaphragms and lubricant gel have lower rates of HIV or STI infection than do their non-diaphragm and gel counterparts. Additionally, we are investigating the long-term acceptability of the diaphragm in this study population.

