**Potential associations between HPV infection and HIV acquisition**. The immune system plays an important role in the natural history of HPV infection. Over 70 types of HPV have been identified, of which over 30 can infect genital epithelium. HPV infection occurs after genital contact and can result in a spectrum of disease encompassing genital warts, precancerous changes known as dysplasia, and invasive cancer. Typically, however, HPV infection is transient, clinically unapparent, resolves spontaneously, and results in subsequent protection against re-infection with that particular HPV type 37. These observations explain the excitement regarding potential HPV vaccines for preventing cervical cancer 54. Consistent with a pivotal role for the immune system in combating HPV infection are clinical observations that immunocompromised individuals are more likely to be infected with HPV, to harbor multiple HPV types, to develop precancer as a result of HPV infection, and to recur after therapy 55-58. The finding of dense infiltrates of lymphocytes in regressing genital warts also argues that the local immune response plays an important role in the natural history of genital warts 59. The immunological activity resulting from HPV infection may increase the risk of vaginal acquisition of HIV by increasing the local presence of immune cells susceptible to HIV infection.

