All HPV tests will be reported as positive for high-risk types, positive for low-risk types, positive for both, or negative for both. High-risk types will be defined as the presence of types 16, 18, 26, 31, 33, 35, 39, 45, 51, 52, 53, 56, 58, 59, 66, 68 and 73 33. Low-risk types will be defined as 6, 11, 40, 42, 54, 61, 70 and 72 33. If the beta-globin control is positive but no HPV is detected, the specimen will be considered “negative.”

**Statistical methods and analyses.** HPV prevalence will be estimated as the observed proportion positive, and associated precision summarized using a 95% exact binomial confidence interval. Incidence of HPV during follow-up will be investigated using survival analysis techniques appropriate for grouped or discrete time outcomes to account for intervals between visits. Initial analyses will include incidence over follow-up of particular types or groups of types among women confirmed to be negative at the baseline visit and will be summarized using life table estimates and 95% confidence intervals. We will use a similar approach in investigating persistence by examining differences in clearance among prevalent positives in both randomized groups. To accommodate repeated episodes of infection and clearance for high-risk types, we will also investigate the use of Markov models for panel data, taking negative and positive HPV tests at study visits as the observed states. These models will allow all available follow-up data to be used, provide direct estimates of the transition probabilities between positive and negative states and allow time-varying risk factors to be investigated using a proportional hazards model similar to those described above. Outcomes of viral load and cytologic and histologic abnormalities will be analyzed similarly.

For study aim #4, we will compare the prevalence rates of HPV (e.g., all HPV types, low-risk, types, high-risk types) between sero-converters and non-sero-converters using matched analysis controlled for confounders. We will separately evaluate the potential association between sero-conversion and HPV viral load using a 3-to-1 control-to-case ratio rather than the entire cohort of non-sero-converters since this assay is relatively expensive to perform.

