**Statistical power.** For study aims #1-3, we calculated minimal detectable relative hazards for the main study outcomes based on the sample size of 2,200 enrollees with a 10% loss-to-follow-up rate, a power of 80% and a significance level of 5% (one-tailed alpha=0.05) using the log-rank test. We chose one-sided tests for this analysis since we do not believe that diaphragms increase risk of HPV outcomes. We performed analyses over a range of plausible prevalence rates of HPV (up to 40% for all types and as low as 20% for high-risk types) and evaluation periods (12 to 24 months). Prior studies of Zimbabwean sero-negative women have indicated a prevalence of HR HPV types of 28% 64. We assumed an annual HR HPV incidence rate of 8% and an annual clearance of 65% in the non-diaphragm arm based on studies from a high-risk area of Brazil 65. The prevalence of cytologic abnormalities was estimated at 15% and incidence at 10% per year in this high-risk population in the non-diaphragm arm. High-grade cervical intraepithelial neoplasia (CIN 2 or worse) prevalence was estimated at 5.9% based on a prior cross-sectional study in Zimbabwe 64. Assuming a cytology sensitivity of 62% 64 and an annual incidence rate of 0.5%, we estimated a prevalence of CIN 2 or worse of 3% by the end of the study in the non-diaphragm arm. For study aim #4, we assumed that 88 women would sero-convert to HIV-positive over the course of the study. We determined the minimal detectable odds ratios for a range of prevalence rates of predictors (e.g., HPV) at 80% power and one-tailed alpha of 0.05.

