Table 1 details all power analyses for study aims #1-3. Under a variety of assumptions, we will have power to detect 16-37% reductions in incidence and persistence of HPV between the diaphragm group and the non-diaphragm group. We will also have power to detect at least a 26% reduction in incidence of cytological abnormalities. We will have less power to be able to detect differences in biopsy-proven CIN 2 or worse (a secondary study aim): a minimum 63% reduction with diaphragm use must be demonstrable for us to be able to detect a statistically significant effect. For study aim #4, we will have adequate power to detect differences in HPV prevalence between sero-converters (cases) and non-sero-converters (controls) if control prevalence rates are 20-40% and cases have at least 2.2 times the prevalence of HPV (Table 2). We believe that we will have adequate power for this analysis; a prior study, for example, has shown that in Zimbabwean women, the prevalence of HR HPV types is over two-fold greater in HIV-positive women (64%) compared to HIV-negative women (28%) 64. Our main hypothesis for study aim #4 involves evaluating a variety of predictors with various prevalence rates (e.g., all HPV types, low-risk, types, high-risk types), and we will have similar power to detect differences for other predictors in this range.

**Table 1:** Least detectable hazard ratios for various HPV-related outcomes over time assuming a sample size of 2,200 enrollees with a 10% loss-to-follow-up rate, a power of 80% and a one-tailed alpha=0.05)

| **Study Aim** | **Outcome** | **Baseline prevalence** | **Observation period (months)** | **Least detectable Relative Hazard** |
| --- | --- | --- | --- | --- |
| **#1** | **HPV incidence**  All types  High-risk types |  | | |
| 40% | 12 | 0.63 |
| 20% | 24 | 0.74 |
| **#2** | **HPV persistence**  All types  High-risk types |  | | |
| 40% | 12 | 0.77 |
| 20% | 24 | 0.84 |
| **#3** | **Cytologic abnormality incidence** | 15% | 24 | 0.74 |
| **Secondary** | **Cervical intraepithelial neoplasia incidence** | 4% | 24 | 0.37 |

**Table 2:** Study aim #4 power: least detectable odds ratios for risk factor prevalences of 10-40% assuming 88 sero-converters and 2,112 non-sero-converters (power=80%, one-tailed alpha=0.05)

| **Risk factor prevalence (e.g., HPV)** | **Least Detectable Odds Ratio** |
| --- | --- |
| 10% | 2.8 |
|  |  |
| 20% | 2.3 |
|  |  |
| 30% | 2.2 |
| 40% | 2.2 |

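### HPV sub-study Aim 3 measures abnormal cytology at one exit Pap, and its detectable hazard of 0.74 holds only if every exit is at 24 months and nothing regresses

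*Protocol*

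**What the plan says.** Appendix 16.2, Study Hypotheses and Specific Aims, makes incidence of cytologic abnormality the subject of Aim 3 and fixes the sampling: "Women will receive cytologic evaluation at enrollment and exit. We will determine the effect of diaphragm use on the rates of cytologic abnormalities." The visit list under Methods and Chart A agree: cytology at the first and last visits only, while HPV is tested at every visit. The sample-collection text and the note to Chart A place exit anywhere from 12 to 24 months, depending on enrolment date.

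Statistical methods and analyses describes grouped or discrete-time survival methods and life tables for HPV incidence, and says Markov panel models will be investigated for repeated infection and clearance. It then adds: "Outcomes of viral load and cytologic and histologic abnormalities will be analyzed similarly."

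Statistical power uses the log-rank test with a "sample size of 2,200 enrollees with a 10% loss-to-follow-up rate, a power of 80% and a significance level of 5% (one-tailed alpha=0.05". For cytology the inputs are: "The prevalence of cytologic abnormalities was estimated at 15% and incidence at 10% per year in this high-risk population in the non-diaphragm arm." The result is given as: "We will also have power to detect at least a 26% reduction in incidence of cytological abnormalities." Table 1 prints the same result as 0.74 with an observation period of 24 months.

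**The concern.** A woman in the at-risk set (normal cytology at enrolment) has a single scheduled later reading. The six-month repeat smears in Chart B follow an ASCUS or LSIL result, so they mainly concern women already abnormal at enrolment. The exit reading records whether an abnormality is present then, so it depends on duration as well as onset. Grouped-time methods handle an unknown onset time when the event stays visible once it has occurred; they do not recover an abnormality that came and went.

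The power figure counts every onset over a full 24 months in every at-risk woman. The design falls short of that in two ways: many women leave before 24 months, and any abnormality that regresses before exit goes unseen. At stake is a stated power that the sampling does not deliver, and an aim labelled incidence when the endpoint is abnormality at exit.

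**Working it through.** **Inputs from the protocol.** 2,200 enrollees, 10% loss, 15% prevalent at baseline, 10% per year incidence in the non-diaphragm arm, one-tailed 5%, 80% power, log-rank (Appendix 16.2, Statistical power); 24 months (Table 1); 1:1 allocation (Trial Abstract); exit at 12 to 24 months (Appendix 16.2).

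**1. Reproduce 0.74.** At risk: 2,200 × 0.90 × 0.85 = 1,683, or n = 841.5 per arm. Control cumulative incidence over two years: 1 − exp(−0.2) = 0.181. Solving the Schoenfeld formula for 80% power, one-sided 5%, gives a hazard ratio of 0.738 (Freedman 0.736). With yearly compounding (0.19) they are 0.744 and 0.742. All round to 0.74.

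Check at 0.74: treated cumulative incidence is 1 − exp(−0.148) = 0.138; events = 841.5 × (0.1813 + 0.1376) = 268; power = Φ(√(268/4) × 0.301 − 1.645) = 79.4%.

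**2. One exit Pap, all at 24 months, no regression.** Compare two proportions, one-sided:

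power = Φ{[p₁ − p₂ − 1.645 √(2p̄(1 − p̄)/n)] / √([p₁(1 − p₁) + p₂(1 − p₂)]/n)}

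With p₁ = 0.1813 and p₂ = 0.1376, power is 79.0% and the detectable hazard ratio 0.736. The single smear costs almost nothing by itself.

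**3. Exits at 12 to 24 months, no regression.** Assume exits spread evenly. The mean of 1 − exp(−λt) over t from 1 to 2 years is 1 − (e^(−λ) − e^(−2λ))/λ. This gives p₁ = 0.139 at λ = 0.10 and p₂ = 0.105 at λ = 0.074. Power at 0.74 is 69% and the detectable hazard ratio 0.70. Placing every exit at 18 months gives the same two results.

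**4. Regression before exit.** The protocol gives no rate, so r is an assumption. With onset rate λ, regression rate r and time t, exit prevalence among women normal at enrolment is λ/(λ + r) × (1 − exp(−(λ + r)t)), averaged over t from 1 to 2 years for spread exits. The same r is used in both arms.

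| r per year (assumed) | 24 months: control prevalence | Power at 0.74 | Detectable HR | 12–24 months: control prevalence | Power at 0.74 | Detectable HR |
|---|---|---|---|---|---|---|
| 0 | 18.1% | 79% | 0.74 | 13.9% | 69% | 0.70 |
| 0.10 | 16.5% | 75% | 0.72 | 12.9% | 66% | 0.69 |
| 0.50 | 11.7% | 61% | 0.67 | 9.8% | 55% | 0.65 |
| 0.57 | 11.0% | 59% | 0.66 | 9.4% | 54% | 0.64 |
| 0.65 | 10.4% | 57% | 0.65 | 8.9% | 52% | 0.63 |
| 1.05 | 7.8% | 47% | 0.61 | 7.1% | 44% | 0.59 |

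The 0.57 is what 15% prevalence and 10% per year incidence imply under an assumed steady state: 0.10 × 0.85/0.15 = 0.57. The last two rows borrow the appendix's 65% annual clearance of high-risk HPV, read as a rate (0.65) or as a yearly proportion (−ln 0.35 = 1.05).

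**5. Direction of the comparison.** At a hazard ratio of 0.74 with all exits at 24 months, the exit-prevalence ratio stays between 0.753 and 0.759 for r from 0 to 1.05. At r = 0.57, for example, it is 0.0834/0.1105 = 0.755.

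**The case against.** The strongest reply is that 0.74 is correctly computed, that a single exit smear at 24 months gives practically the same figure, and that the whole regression loss rests on a rate found nowhere in the protocol. All of that stands. The steady state behind 0.57 is not claimed in the appendix. The remark "Typically, however, HPV infection is transient, clinically unapparent, resolves spontaneously" and the 65% clearance concern HPV infection, not cytology. The 10% per year may already be partly net of regression if it came from spaced smears. For these reasons regression belongs in a sensitivity range, not in a single replacement figure.

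Zero regression is nevertheless hard to reconcile with the appendix's own inputs. At 10% per year, 15% prevalence would be reached in −ln(0.85)/0.10 = 1.6 years, yet eligible women are 18 to 49. Chart B also provides for a repeat smear that has returned to normal.

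A second reply is that the planned methods already include grouped-time analysis and that the Markov models allow for reversible states. That stands as far as it goes. Women abnormal at enrolment, with their repeat smears, could inform regression, and optional Paps exist in the main trial (sections 9.4 and 9.10). But women normal at enrolment still have one scheduled later reading, and the power statement uses none of this.

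A reader might infer that the exit comparison cannot bear on incidence at all, or that 0.74 is unattainable because there is only one smear. The documents support neither reading. Step 2 shows that the single smear alone costs almost nothing. Step 5 shows that exit prevalence tracks the hazard ratio closely when regression is equal across arms.

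**Conclusion.** The point holds as a matter of endpoint definition and stated power. Aim 3 observes abnormal cytology present at exit among women normal at enrolment, not all incident abnormality. The 26% figure requires every exit Pap at 24 months and no regression, and the appendix itself contradicts the first condition.

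On the protocol's inputs plus evenly spread exits, power at 0.74 is about 69% and the detectable hazard ratio about 0.70. Regression lowers this further by an amount the documents do not fix: for 0.1 to 1.05 per year, the detectable hazard ratio is 0.72 to 0.61 with all exits at 24 months, or 0.69 to 0.59 with exits over 12 to 24 months. The steady-state case gives 59% or 54% power at 0.74. The damage is to power and wording, not to the direction of the comparison, and it is confined to one aim of a sub-study.

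**What to change.** In Appendix 16.2:

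- Define the Aim 3 endpoint as abnormal cytology at the exit Pap among women with normal enrolment cytology.
- Compare arms with a complementary log-log (grouped-time) model that includes time from enrolment to exit Pap, in place of the log-rank test.
- In Statistical power and the cytology row of Table 1, replace 0.74 and 26% with a detectable hazard ratio no better than about 0.70 (30% reduction), based on exit at 12 to 24 months. State the assumed exit distribution, and add a sensitivity range for regression with its assumptions, as in the table above.

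No extra smears, visits or data are needed. The cost is some rewording, one recomputed table row and a less favourable stated figure.
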